### Secondary outcomes

These include 36-month change in quality of life using the World Health Organization Quality of Life Brief Version (WHOQOL-BREF) [27], visual functioning (21-item Rasch version of the Indian Vision Function Questionnaire) [28], depression (Patient Health Questionnaire-9) [29], physical activity (International Physical Activity Questionnaire) [30], social interaction and networking (Social Networking Index questionnaire) [24], and falls risk (Quick Screen falls assessment) [31]. The trial will also assess the cost-effectiveness of the intervention as total intervention cost per quality-adjusted life years gained in the intervention group. The Client Service Receipt Inventory will be used to assess the resource use for medical care by the study participants [32] (Table 1).

**Table 1 Tab1:** Schedule of assessments with details on location, personnel, and frequency

	Instrument name	Details	Baseline	Year 1	Year 2	Year 3
1	Personal and demographic information questionnaire	It includes age/gender, level of education, marital status, and income	✓			
2	World Health Organization Quality of Life Brief Version (WHOQOL-BREF) [27]	It has 26 items and covers four domains of quality of life: a) physical health, b) psychological well-being, c) social relationships, and d) environment	✓	✓	✓	✓
3	Indian Vision Function Questionnaire [28]	It has 20 questions covering visual functioning and mobility domains	✓	✓	✓	✓
4	Patient Health Questionnaire (PHQ9) for depression [29]	It has nine questions with scores of 0–3 points per question, for a total score of 0–27 points	✓	✓	✓	✓
5	Social Networking Index questionnaire [24]	It has 12 questions that assess the number of high-contact roles (network diversity), number of people in social networks, and embedded networks	✓	✓	✓	✓
6	International Physical Activity Questionnaire (IPAQ) Short form [30]	It has 7 questions and measures a 7-day recall of physical activities	✓	✓	✓	✓
7	Risk factors (alcohol consumption and smoking)	Includes questions on present and past smoking and alcohol consumption	✓	✓	✓	✓
8	Hindi Mini mental State Examination (HMSE) [19]	It is a 22 questions-based scale with a maximum score of 31	✓			
9	Ocular history and systemic health questionnaire	It includes questions on previous surgeries, use of spectacles, and duration of use. Systemic health questionnaire includes information on hypertension, diabetes and other non-communicable diseases	✓	✓	✓	✓

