10	Longitudinal Aging Study in India–Diagnostic Assessment of Dementia; LASI-DAD cognitive test battery [25, 26]	It covers the key cognitive domains: memory, attention/speed, orientation, language function, visuospatial skills, executive function, numerical ability, and retrieval fluency	✓	✓	✓	✓
11	Client Service Receipt Inventory for healthcare costs [32]	This collects information on the whole range of services, including estimating the costs of service receipt	✓	✓	✓	✓
12	Clinical Falls Risk Assessment: Quick screen questionnaire [31]	It assesses five factors related to falls: history of falls in the last 12 months, regular use of four or more medications, vision, peripheral sensation, balance, time reaction, and lower limb strength	✓	✓	✓	✓

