Three-year change from baseline in quality of life, visual functioning, depression, falls, social interaction and networking, and physical activity will be the secondary outcomes. Rasch analysis will be conducted to derive interval scores from quality of life and vision-related quality-of-life instruments. A mixed-effects binomial regression with a log link will be used to estimate the relative risk, and a binomial model with an identity link for estimating the risk difference will be used to assess between-group differences in change in depression. A mixed-effects linear regression with an identity link will be used to estimate the between-group mean difference in change in falls. Participants will be placed into three categories of physical activity and social interaction for these analyses as previously described [30, 34].

The cost-effectiveness analysis will estimate the expected incremental cost per unit difference in the cognitive factor scores between the intervention and the control groups. A health and social care perspective will be used for the analysis. A Markov model will be developed, allowing the comparison of the CLEVER intervention with alternative interventions for preventing cognitive decline. An “in-trial” analysis that compares the costs and outcomes of the two study groups for the time horizon of the trial will be conducted. Multinomial logistic regression will be used to adjust for potential confounders. Odds ratios and their 95% confidence intervals will be reported.

Statistical significance of all results will be assessed at the conventional level of *p* < 0.05 (two-tailed). Stata (V.16, Stata Corp, College Station, Texas, USA) will be used for all statistical analyses.

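### Change in PHQ-9 depression score is assigned only binomial models, which need a yes/no status the article does not name; separately, the falls-risk score contains vision, which spectacles can change directly

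*Protocol article*

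**What the plan says.** **Depression.** Under Secondary outcomes, the protocol article lists 36-month change on several instruments, including the PHQ-9 for depression. Table 1 describes that instrument: "It has nine questions with scores of 0–3 points per question, for a total score of 0–27 points". The section Data management and analysis plan repeats the definition: "Three-year change from baseline in quality of life, visual functioning, depression, falls, social interaction and networking, and physical activity will be the secondary outcomes". It then names two models for depression. The first is "A mixed-effects binomial regression with a log link will be used to estimate the relative risk"; the second is "a binomial model with an identity link for estimating the risk difference will be used to assess between-group differences in change in depression". No linear model is named for depression. The same paragraph does state a three-category grouping for physical activity and social interaction, but no grouping or threshold for depression.

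**Falls.** Under Secondary outcomes the measure is falls risk by the Quick Screen assessment. The Table 1 row for that instrument lists, among other components, "history of falls in the last 12 months, regular use of four or more medications, vision, peripheral sensation, balance". The row announces five factors but goes on to list seven. The analysis plan drops the word risk and says: "A mixed-effects linear regression with an identity link will be used to estimate the between-group mean difference in change in falls".

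**The concern.** For depression, the measure and the model are of different types. A relative risk and a risk difference describe a yes/no state, while a change in a 0–27 score is numeric and can be negative. As written, the analysis cannot be run on the stated outcome. Someone must first choose a binary endpoint, and that choice affects both the estimate and the power. The trial is open-label and its personnel are unmasked, so the endpoint should be fixed in writing before outcome data are examined.

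For falls, the question is what the score measures. Participants are enrolled for vision impairment that spectacles correct, the intervention is spectacles, and vision is a listed component of the score. A difference between arms could therefore come partly or wholly from that component. Because the analysis plan calls the outcome falls, such a difference could be reported as an effect on falling.

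**Working it through.** **1. Type of the depression outcome.** The PHQ-9 total runs from 0 to 27 (Table 1), so its change from baseline runs from −27 to +27. A binomial response is 0 or 1. Dichotomising at each visit and then taking the change gives −1, 0 or +1, which is still not binomial. A binomial model needs a different endpoint, such as depressed status at 36 months, and the article names none.

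**2. Information lost by dichotomising (illustration).** Assume a normal score and a small shift in its mean. With p the case rate, z the matching normal quantile and φ the normal density, efficiency relative to the continuous analysis is φ(z)² / [p(1 − p)].

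| Case rate p | Relative efficiency | Equivalent loss of participants |
|---|---|---|
| 50% | 0.637 | 36% |
| 20% | 0.490 | 51% |
| 10% | 0.342 | 66% |

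**3. The same point at this trial's size.** The plan's own sample size comes first. Read the 29% effect size as a standardised difference of 0.29, with 90% power and two-sided 0.05:
- The normal formula gives 250 per arm.
- Loss of 13% a year for three years leaves 0.87³ = 0.6585, a loss of 0.3415.
- 250 / 0.6585 rounds up to 380 per arm, or 760 in total, as stated. The t-test version gives 764.

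The sample size therefore reproduces, and about 250 per arm complete. Now suppose the PHQ-9 also shifted by 0.29 SD. This borrows the primary outcome's effect size purely for illustration. Analysed as a score, power is 90.0%. If the score is cut so that a proportion p of controls are cases, the intervention proportion is 1 − Φ(z₁₋ₚ + 0.29):

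| Control | Intervention | Relative risk | Risk difference (points) | Power |
|---|---|---|---|---|
| 5% | 2.65% | 0.53 | −2.35 | 27.7% |
| 10% | 5.80% | 0.58 | −4.20 | 41.3% |
| 20% | 12.89% | 0.64 | −7.11 | 57.4% |
| 30% | 20.77% | 0.69 | −9.23 | 66.0% |
| 50% | 38.59% | 0.77 | −11.41 | 73.0% |

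The underlying shift is the same in every row. Only the cut differs.

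**4. Falls risk.** A linear mixed model for mean change in a numeric multi-component score is acceptable, so the model needs no correction. For the vision component, let w be its weight in the score, and let q_C and q_I be the proportions failing it in the control and intervention arms. If nothing else changes, the arms differ by w(q_C − q_I). The article gives none of these three quantities. It does not say how items are scored, whether vision is tested with spectacles worn, or whether at distance or near. The inclusion criteria also admit people with near impairment only, whose near spectacles need not change a distance item. The direction of the overlap is clear; its size cannot be computed.

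**The case against.** **On depression,** the fairest defence is that the article says change in depression, not change in PHQ-9 score, and that the 0–27 range only describes the instrument. A mixed-effects binomial model of repeated depressed/not-depressed status could estimate a difference in change on the risk scale, and a cut-off is commonly left to a SAP. Part of this stands: a binary endpoint would be legitimate, and an absent cut-off alone would be no finding. But the article itself fixes both a change-from-baseline outcome on a numeric instrument and a risk-scale model. It does not say that a binary status is intended, although it states a grouping for two other outcomes in the same paragraph. The two statements need reconciling, and the score analysis is the more powerful way to do so.

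The efficiency figures are also generic. That is correct: the article gives no PHQ-9 distribution, prevalence or threshold, so they are illustrations only.

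**On falls,** vision is a genuine part of falls risk, so improvement through vision may be a mechanism rather than an artefact, and removing an item alters a cited instrument. This stands as a reason to keep the total and add an analysis, not to replace it.

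**Stronger readings that do not hold.**
- A reader might infer that the falls model is also wrong, or that the depression and falls models were transposed, since fall history is an event. The defined outcome is Quick Screen falls risk, not any fall, and a linear model suits a numeric score. Nothing in the text indicates a swap.
- A reader might infer that spectacles determine up to one point of the score. That presumes one point per item, and the article gives no scoring.

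**Conclusion.** The depression point holds. The article's only models for change in depression do not match a 36-month change on a 0–27 score, and the binary status they require is not named. This follows from the text and needs no calculation. The cost of dichotomising is illustrative: efficiency of about 64%, 49% or 34% at case rates of 50%, 20% or 10%, assuming a normal score.

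The falls point holds in a limited form. The falls-risk score includes a component that the intervention can change directly, so a difference between arms need not reflect less falling or lower non-visual risk. Its size is unknown. The linear model for falls risk is acceptable.

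Both points concern secondary outcomes. The primary analysis and the sample size of 760 are unaffected. The corrections should be made before outcome data are analysed.

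**What to change.** **Depression.** Make the main analysis a linear mixed model of the PHQ-9 total, with baseline PHQ-9 as a covariate and the mean difference between arms at 36 months as the estimate. Keep the relative risk and risk difference as a supportive analysis of a binary status at 36 months, with its definition written down in advance.

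**Falls risk.** Keep the linear mixed model for the Quick Screen total. Add a pre-specified analysis with the vision item removed, and report fall history separately. In the analysis plan, call the outcome falls risk rather than falls, and reconcile the five and seven factors in Table 1.

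**Cost.** Wording in the protocol or SAP only. Table 1 schedules both instruments at baseline and at each of the three annual visits, so no new data are needed. The small downside is that the score without vision is not the published total, which is why the total should still be reported.

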## Discussion

CLEVER is the first trial anywhere to investigate the potential cause-and-effect relationship between provision of spectacles and the rate of cognitive decline in an elderly population. Spectacles are one of the most cost-effective interventions in all of health care, and uncorrected near and distance refractive error are the most common cause of VI world-wide. If spectacles are proven to slow cognitive decline, then service delivery programs can be developed to address the twin public health problems of VI and cognitive impairment. The impact on the health of an aging global population will be substantial, especially for the 70% living in LMICs, who currently lack proven, low-cost treatments to delay or prevent dementia.

The multidisciplinary team of specialists, including ophthalmologists, optometrists, cognitive neurologists, social investigators, and neuropsychologists is an added strength of the trial.

## Conclusions

The randomised, controlled design of CLEVER will provide robust evidence for the impact of low-cost vision care on cognitive health. The information gained from a positive trial result would contribute significantly to the goal of healthy aging in India and other LMICs.

## Data Availability

Not applicable.

## Abbreviations

CLEVER: Cognitive Level Enhancement through Vision Exams and Refraction
CSRI: Client Service Receipt Inventory
CTU: Clinical trial unit
DMEC: Data Monitoring and Ethics Committee
logMAR: Logarithm of minimum angle of resolution
LASI-DAD: Longitudinal Aging Study in India-Diagnostic Assessment of Dementia
LVPEI: L V Prasad Eye Institute
HbA1C: Haemoglobin A1C
HMSE: Hindi Mini-mental Status Examination
IPAQ: International Physical Activity Questionnaire
LMICs: Low- and middle-income countries
NIMHANS: National Institute of Mental Health and Neurosciences
OCT: Optical Coherence Tomography
PHQ9: Patient Health Questionnaire-9
QUB: Queen’s University Belfast
SNI: Social Networking Index
VA: Visual acuity
VI: Vision impairment
WHOQOL-BREF: World Health Organization Quality of Life Brief Version
